### Study objectives

The Teen TB study has three main objectives. The first is to evaluate the relationship between baseline lung imaging (advanced and point of care) and respiratory function in adolescents with TB disease. We aim to test the hypothesis that imaging at the time of diagnosis can predict future lung function. The second objective is to explore the psychosocial experience of adolescents affected by drug-susceptible (DS) and MDR-TB and evaluate if the diagnosis of TB is associated with experiences of stigma. The third objective is to explore how pubertal hormones and viral coinfections (notably cytomegalovirus (CMV)) influence the immune response to *Mtb*. We hypothesise that as adolescents pass through puberty, they generate an increasingly pronounced myeloid inflammatory response to *Mtb*.

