### Respiratory function assessment

Forced expiratory volume in 1 second (FEV1), forced vital capacity (FVC) and the FEV1/FVC ratio will be carried out using a hand-held NDD EasyOne PC (Switzerland) spirometer at baseline in all adolescents and again at 2 weeks and 2 months in those with TB disease. A minimum of three trials up to a maximum of eight attempts will be carried out per participant and at least three acceptable, reproducible best quality curves will be selected. The best value of three will be reported. Four hundred micrograms of salbutamol will be administered via spacer and testing will be repeated after 15 min to assess reversibility. Criteria for acceptability and repeatability of the spirometry curves will be based on European Respiratory Society (ERS)/American Thoracic Society (ATS). Global Lung Initiative reference ranges will be used using the category ‘other’ to reflect the South African population.^25 26^

The portable THORASYS tremoFlo C-100 Airwave Oscillometry System will be used for additional assessment of pulmonary function. The TremoFlo is a tidal breathing technique that measures airway resistance and reactance and allows for detailed insights into small airway disease. All participants will have oscillometry at baseline, while those with TB disease will have this repeated at 2 weeks, 2 months and 12 months. Oscillometry will be done pre-bronchodilation and post-bronchodilation as described for spirometry.

In collaboration with the Tygerberg Lung Function Laboratory, all individuals with TB exposure but without disease will undergo a full lung function assessment as soon after recruitment as possible. For those with TB disease, the evaluation will take place at 2 months and 12 months post recruitment. This will include spirometry with pre-bronchodilator and post-bronchodilator measurement, diffusion capacity and plethysmography. These tests will be conducted according to ERS/ATS guidelines and local hospital protocols.

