#### Assessment of study endpoints/primary objectives

Descriptive analysis will be used to characterise the study populations, to compare the TB case and TB-exposed groups and aid in identifying differences between groups with respect to potential confounders. Categorical variables will be expressed as percentages and continuous variables will be expressed as mean±one SD or median with IQR, depending on the distribution of the data.

In those with TB disease, we will categorise disease on CXR as severe and non-severe, using established criteria^29^ and will compare mean z-score of FVC, FEV1 and FEV1/FVC ratio at 2 months and 12 months in those with severe and non-severe disease using a paired sample t-test. We will also evaluate the relationship between severe and non-severe disease on CXR with other measures of functional tests (oscillometry, diffusion capacity, plethysmography, 6MWT and SGRQ). We will perform similar analyses evaluating the ability of ultrasound, CT and ^18^F-FDG PET-CT to predict different measures of lung function at 2 months and 12 months. We will compare the lung function of adolescents with TB disease and those with TB exposure using multivariable logistic regression to adjust for potential confounders and to determine the impact of TB on lung health. From a radiology perspective, we will evaluate the ability of CXR and lung ultrasound to identify findings as seen on CT chest (considered as the imaging ‘gold standard’ for this analysis) using either contingency tests or receiver operating characteristic (ROC) analysis, where appropriate.

Further multivariable analyses will be performed to explore the impact of pubertal hormones on inflammatory cytokines and how the inflammatory cytokines of adolescents with TB disease and TB exposure differ. Immune responses to viral coinfections in participants with TB disease and those with TB exposure will also be compared using regression analysis. Analyses will be performed using STATA (V.17 STATA Corp.).

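### A paired t-test is named for comparing severe with non-severe cases, who are different adolescents, so the imaging hypothesis has no suitable named test

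*Protocol article*

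**What the plan says.** All of this is in the Protocol article.

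- **Study objectives**, first objective: "We aim to test the hypothesis that imaging at the time of diagnosis can predict future lung function".
- **Assessment of study endpoints/primary objectives**, grouping: "In those with TB disease, we will categorise disease on CXR as severe and non-severe, using established criteria".
- Same section, outcome: the investigators "will compare mean z-score of FVC, FEV1 and FEV1/FVC ratio".
- Same section, visits and test: "at 2 months and 12 months in those with severe and non-severe disease using a paired sample t-test".
- Same section, extension to other imaging: "We will perform similar analyses evaluating the ability of ultrasound, CT and" PET-CT to predict lung function at the same two visits.
- **Respiratory function assessment**, on full laboratory lung function: "For those with TB disease, the evaluation will take place at 2 months and 12 months post recruitment".

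No matching of severe to non-severe adolescents is described in any section.

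**The concern.** A paired t-test works on one difference per linked pair. Severity on chest X-ray places each case in exactly one of two groups, so a severe adolescent has no partner in the non-severe group, and the groups will usually differ in size. The only natural pairing in the data is the same adolescent at 2 and at 12 months. That pairing supports a question about change, whereas the hypothesis asks whether adolescents with worse imaging at diagnosis later have worse lung function.

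This is the only test the article names for predicting lung function from imaging, and the analyses for ultrasound, CT and PET-CT are described as similar to it. If it is followed literally, the first objective gets either an inefficient, order-dependent result or an answer to another question. If it is not followed, the method is chosen after the data are in.

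**Working it through.** **Step 1. The plan's own figure.** The only sample-size calculation (Power and sample size) compares cases with healthy controls on FEV1/FVC: means 90% and 100%, SD 15%, power 90%, alpha 0.05, 47 per group. Taking alpha as two-sided:

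n per group = 2 × [SD × (z₀.₉₇₅ + z₀.₉₀) / difference]² = 2 × [15 × (1.960 + 1.282) / 10]² = 47.28

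This reproduces the stated 47 (strict rounding up gives 48; power at 47 is 89.8%). It is a calculation for two independent groups. It does not size the severe versus non-severe comparison.

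**Step 2. The two readings of the sentence.**

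| Reading | What is paired | Does the test apply? | Does it address the hypothesis? |
|---|---|---|---|
| A. Severe versus non-severe at each visit | Nothing; different adolescents | No, unless pairs are invented | Right contrast, wrong test |
| B. 2 versus 12 months within each severity group | The same adolescent twice | Yes | No; it measures change |

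The sentence that follows in the article relates severe and non-severe disease to the other functional tests, which points to reading A.

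**Step 3. Reading A, cost of invented pairs.** Inputs: 50 cases (Power and sample size) and two-sided alpha 0.05. Two inputs are assumptions because the article gives neither for this comparison: a true difference d = 10/15 = 0.667 SD, borrowed from the case-control calculation, and the severe/non-severe split, varied from 25/25 to 40/10. Power comes from the noncentral t distribution.

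- Independent test: noncentrality = d × √[n₁n₂/(n₁+n₂)], df = n₁ + n₂ − 2 = 48.
- Arbitrary pairs: m = size of the smaller group, correlation 0, so the SD of a difference is √2 SD; noncentrality = d × √(m/2), df = m − 1.

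| Split | Noncentrality, independent | Power, independent | Pairs (cases dropped) | Noncentrality, pairs | Power, pairs |
|---|---|---|---|---|---|
| 25/25 | 0.667 × √12.5 = 2.36 | 63.7% | 25 (0) | 0.667 × √12.5 = 2.36 | 61.9% |
| 30/20 | 0.667 × √12 = 2.31 | 61.9% | 20 (10) | 0.667 × √10 = 2.11 | 51.6% |
| 35/15 | 0.667 × √10.5 = 2.16 | 56.2% | 15 (20) | 0.667 × √7.5 = 1.83 | 39.8% |
| 40/10 | 0.667 × √8 = 1.89 | 45.5% | 10 (30) | 0.667 × √5 = 1.49 | 26.6% |

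**Step 4. Reading B, what the within-group test detects.** In a simulation with 25 adolescents per group, the severe group had a constant deficit of 0.667 SD at both visits, with within-person correlation 0.5 or 0.8 (5,000 runs each). The paired test of 2 versus 12 months in the severe group rejected in 4.8% and 4.7% of runs, which is simply alpha. A two-sample test at 12 months on the same data rejected in 64.1% and 63.6%. A lasting deficit that imaging predicts is therefore invisible to the paired test.

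**Step 5. What the corrected test can show.** With an independent test in 50 cases, the difference detectable with 80% power is 0.81 SD at 25/25, 0.88 SD at 35/15 and 1.01 SD at 40/10. If only 40 cases were evaluable (an assumption), power at 0.667 SD would be 53.8% at 20/20 and 37.6% at 32/8.

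**The case against.** The strongest reply is that the sentence is ambiguous. Full lung function is measured in cases at exactly the two visits named, so the authors may have meant a within-person comparison in each severity group, for which a paired test is correct. This stands as a reading of the words. It does not rescue the plan, because that comparison leaves the prediction hypothesis without a named test. A change in one group but not in the other would not show that the groups differ either.

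Three further points limit how far the criticism goes:

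- **Type I error.** Pairing in an order unrelated to the outcome does not bias the test. In a simulation with a 35/15 split and no true difference (20,000 runs), it rejected in 5.1%. The harm under reading A is lost data and an irreproducible result, not false positives.
- **Size of the loss.** At equal split the loss is under 2 percentage points. It becomes large only as the groups become unequal, and the split is unknown.
- **Reach.** The article designates no single primary test, and it says only that the analyses for other imaging are similar. Carry-over of the paired test to them is a natural inference but is not stated.

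It can also be said that any analyst would notice the error when faced with two unlinked groups of different sizes. That is likely, but the replacement method would then be chosen with the data in hand. Nor is this a detail left to a fuller document: a specific test is named, and it does not fit the comparison.

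**Conclusion.** The concern holds. As written, the named test either does not apply (between severity groups) or does not address the hypothesis (within groups over time). That conclusion follows from the design and needs no assumption about effect size.

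The cost in power does rest on assumptions: a 0.667 SD difference, 50 evaluable cases and a split that the article does not give. On those terms, arbitrary pairing loses 1.8 percentage points at 25/25, 10.3 at 30/20, 16.4 at 35/15 and 18.9 at 40/10. Even the correct test has only 46% to 64% power across these splits, so the estimate and its confidence interval will say more than the p-value. The sentence needs correcting before the analysis is run.

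**What to change.** Replace the paired t-test in Assessment of study endpoints/primary objectives with an independent two-sample comparison of z-scores between severe and non-severe cases at each visit: a Welch t-test, or a linear regression of the z-score on severity. Report the severe minus non-severe difference with its 95% confidence interval at 2 and at 12 months. State that the same approach applies wherever ultrasound, CT or PET-CT findings divide the cases into groups. If change between 2 and 12 months is also of interest, name it as a separate within-person question and keep the paired test for that alone.

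Optionally, a single linear mixed model of both visits with severity, visit and their interaction would give both contrasts together; it is not needed to correct the error.

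The cost is one sentence of analysis wording. No new data, visits or participants are required.

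### Objective 1 is worded as prediction of later lung function, but the only analysis named for it compares group means, which shows association and not how well imaging predicts

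*Protocol article*

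**What the plan says.** In the Protocol article, Study objectives, the first objective has two parts. One is to "evaluate the relationship between baseline lung imaging (advanced and point of care) and respiratory function in adolescents with TB disease". The other is a hypothesis: "We aim to test the hypothesis that imaging at the time of diagnosis can predict future lung function".

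Under Statistical analysis, Assessment of study endpoints/primary objectives, the method named for chest X-ray (CXR) is to "compare mean z-score of FVC, FEV1 and FEV1/FVC ratio at 2 months and 12 months in those with severe and non-severe disease". The test specified for this is a t-test, labelled as paired. For the remaining functional tests the text reads "We will also evaluate the relationship between severe and non-severe disease on CXR with other measures of functional tests", with no measure named. For the other modalities it reads "We will perform similar analyses evaluating the ability of ultrasound, CT and" PET-CT to predict lung function at the same two follow-up times.

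The same section does name an accuracy method, but for a different question: "we will evaluate the ability of CXR and lung ultrasound to identify findings as seen on CT chest". The methods listed for that question, with CT as the reference, are given as "using either contingency tests or receiver operating characteristic (ROC) analysis, where appropriate".

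**The concern.** The hypothesis and the sentence on ultrasound, CT and PET-CT both speak of prediction. The analysis attached to them asks whether two groups differ on average. Two groups can differ clearly in mean while their individual values overlap heavily, so a small p-value does not say how far imaging narrows the range of lung function expected for a given adolescent.

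This goes beyond detail that an article might leave out. A method is stated for the hypothesis, and it measures something else. The authors name ROC analysis in the same paragraph, but only with CT findings as the reference, never with lung function as the outcome.

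At stake is how the main imaging result will be read. The Introduction expects the study to have implications for later interventional studies. A report that imaging predicts lung function, resting on a significant mean difference in at most 50 cases, could be taken as evidence that imaging can identify which individuals will have poor lung function.

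**Working it through.** **The plan's own figure.** The sample size section assumes an FEV1/FVC ratio of 100% against 90%, SD 15%, 90% power and alpha 0.05, and states 47 per group. Two-sided normal approximation: n = 2 × (1.960 + 1.282)² × (15/10)² = 47.3. This reproduces 47 (48 if rounded up). It concerns cases against controls. The imaging analyses use the cases only, so at most N = 50.

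**What a just-significant mean difference means within the cases.** The groups being compared are different adolescents, so I use the independent two-sample t-test. (The plan's label of paired is a separate matter.)

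- Critical value: t(0.975, 48 df) = 2.011, so t² = 4.043.
- R² = t² / (t² + N − 2) = 4.043 / 52.043 = 0.078.
- Adjusted R² = 1 − (1 − 0.0777) × 49/48 = 0.058.
- Residual SD as a share of total SD = √(1 − 0.0777) = 0.96.

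These results do not depend on how the cases divide by severity. The next two do, and the document gives no split, so I assume a range:

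| Severe : non-severe | d = t × √(1/n₁ + 1/n₂) | AUC = Φ(d/√2) |
|---|---|---|
| 25 : 25 | 2.011 × √0.080 = 0.57 | 0.66 |
| 10 : 40 | 2.011 × √0.125 = 0.71 | 0.69 |

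Here AUC is the chance that a randomly chosen severe case has the worse z-score of a random severe/non-severe pair, assuming normal distributions. It is not the AUC for classifying lung function as abnormal.

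**With losses.** If 40 cases are evaluable (an assumption), t(0.975, 38 df) = 2.024, R² = 4.098 / 42.098 = 0.097, residual SD is 95% of total, and AUC is 0.67 (20:20) to 0.71 (8:32).

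**Uncertainty at the boundary, N = 50.** Observed r = √0.0777 = 0.279. An approximate Fisher interval is tanh(0.286 ± 1.96/√47) = tanh(0.286 ± 0.286), that is r from about 0 to 0.517, or R² from about 0% to 27%. The p-value alone does not separate negligible from moderate prediction.

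**The case against.** The best defence has four parts.

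- **Wording of the objective.** Its first half asks about a relationship, and a comparison of means suits that. *Predict* is also used loosely in cohort studies for a baseline factor associated with a later outcome. This stands in part. It is why rewording is an acceptable remedy, but it does not make a mean difference a measure of predictive ability.
- **Condensed article.** The choice of R², validation method and bootstrap commonly sits in a fuller plan. This stands for the technical detail. It does not remove the mismatch, because a method is given here for the prediction question and it is one of association.
- **Deciding whether the hypothesis is met.** A reader might infer that the plan would declare it met by imaging that predicts almost nothing. The documents do not support that. They set no significance rule for the hypothesis, mean z-scores by group will be visible, and the boundary result (AUC about 0.66 to 0.69) is weak but not nil. The boundary is also the smallest significant result, not the typical one.
- **Ranking of modalities.** A reader might infer that the plan fails to show which modality predicts better. No passage promises such a ranking for lung function, so the absence of a head-to-head test contradicts no stated objective. Contrasting significant with non-significant modalities would still mislead. If two modalities each correlate 0.30 with the outcome and 0.5 to 0.7 with each other (all assumed, treated as continuous), simulation with 50 cases finds exactly one significant in about 26% to 34% of studies. That is a caution for reporting, not an error in the plan.

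**Conclusion.** The point holds as a mismatch between the wording of the hypothesis and the analysis named for it. With 50 cases, a just-significant mean difference explains about 8% of the observed variance (adjusted 6%) and leaves the residual SD at 96% of the total. These two figures rest only on N = 50 and a two-sided 5% test. The AUC of about 0.66 also assumes equal severity groups and normality. Significance on its own would therefore support a statement of association and only weakly a statement of prediction. The comparison of means need not be withdrawn, since it answers the relationship half of the objective. This should be corrected, but it does not threaten the study's validity.

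**What to change.** In Assessment of study endpoints/primary objectives, add for each modality the proportion of variance in the 2-month and 12-month z-scores that it explains, or the AUC for abnormal lung function under a definition fixed in advance. Give an optimism-corrected estimate (bootstrap or cross-validation), a 95% CI and, for the z-scores, the residual SD. Report these beside the mean differences, and rest any claim of prediction on them.

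The alternative is to replace *predict* with *is associated with* in Study objectives and in the analysis section, and keep the analysis as it is.

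Optional: if the report compares modalities, give the difference in explained variance within the same cases with a CI, and do not contrast significant with non-significant tests. I would not rest the objective 1 conclusion on this. With 50 cases and assumed modality-outcome correlations of 0.5 and 0.3, the true difference in R² is 0.25 − 0.09 = 0.16, and its sampling SD in simulation is about 0.08 to 0.10.

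Cost: a few lines of wording and code, and no new data. The estimates will look modest and their intervals will be wide, as the 0% to 27% interval above shows.

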TB-exposed controls are recruited from the same clinics where individuals with TB disease are recruited, and the contacts of the enrolled cases will also be eligible for inclusion. TB-exposed controls must have been exposed to an infectious DS-TB case within the last 6 months. We will again use the TB-CHAMP platform to aid in identifying adolescents who have been exposed to an infectious pulmonary MDR-TB case in the household within the last 6 months.

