### Statistical analysis

#### Power and sample size

While multiple different analyses are planned for the different components of the study (clinical, immunology, radiology, social science, virology), we calculated the sample size based on ability to detect differences in lung function. Even within this discipline, several lung function parameters will be measured during this study, but sample size calculations were performed based on assumptions related to spirometry. A reduced FVC, compared with age and height reference standards, indicates restrictive lung disease, whereas a reduced FEV1 and FEV1/FVC ratio, compared with reference standards, indicate obstructive lung disease. Both patterns of lung disease have been seen in adults following pulmonary TB. To demonstrate a difference between healthy individuals in our context (assumed to have a FEV1/FVC ratio of 100%; SD: 15%), and adolescents with pulmonary TB disease (assumed to have a ratio of 90%), with 90% power and an alpha of 0.05, we would need 47 adolescents with pulmonary TB and 47 healthy controls. Therefore, we plan to recruit 50 cases and 50 controls given the uncertainty in these estimates and to allow for any lost data or incomplete evaluations.

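### Logistic regression is named for the adjusted case-control comparison of continuous lung function, so the planned model does not estimate the mean difference on which the study was sized

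*Protocol article*

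**What the plan says.** Under *Assessment of study endpoints/primary objectives*, the Protocol article assigns the adjusted lung-function comparison to one model: "We will compare the lung function of adolescents with TB disease and those with TB exposure using multivariable logistic regression". The stated purpose is "to adjust for potential confounders and to determine the impact of TB on lung health". The article does not say which variable is the dependent one, and it defines no threshold for abnormal lung function.

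Under *Power and sample size*, the authors write that "we calculated the sample size based on ability to detect differences in lung function". Healthy individuals are "assumed to have a FEV1/FVC ratio of 100%; SD: 15" per cent, against "adolescents with pulmonary TB disease (assumed to have a ratio of 90" per cent. The conclusion is that "with 90% power and an alpha of 0.05, we would need 47 adolescents with pulmonary TB and 47 healthy controls", and 50 per group are planned.

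*Respiratory function assessment* lists FEV1, FVC, their ratio, oscillometry, diffusion capacity and plethysmography, which are all continuous. For severe versus non-severe disease on chest X-ray, the analysis section itself compares mean z-scores of the spirometric measures.

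**The concern.** The contrast between cases and controls is the one that justifies 50 plus 50 participants, and it was sized as a difference between two means. The model named for its adjusted analysis needs a binary outcome. There are two ways to supply one:

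- Lung function is the outcome and is dichotomised at some threshold. This discards information and gives an odds ratio for abnormality.
- TB status is the outcome and lung function is a predictor. This gives the odds of being a case for a given lung function.

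Neither says by how much lung function is lower in adolescents with TB after adjustment, which is what the stated purpose asks for. At stake are the match between the analysis and the sample size and, under the first reading, a large part of the power.

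**Working it through.** **Inputs.** From *Power and sample size*: means 100 and 90, SD 15, alpha 0.05, power 90%, 47 per group needed, 50 planned. Sidedness is not stated. Assumed here: normal distributions with equal SD in both groups, and the cut-offs in the table, since the article gives none. All figures are before covariate adjustment.

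**1. The plan's own figure.** Two-sided comparison of two means:

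n = 2 × [15 × (1.960 + 1.282) / 10]² = 47.3 per group.

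The stated 47 is reproduced to within rounding. A one-sided test would give 39, so the calculation is a two-sided comparison of means. It is not a calculation for a binary outcome.

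**2. Power for means at 50 per group.** The standardised difference is d = 10/15 = 0.667.

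Power = Φ(0.667 × √(50/2) − 1.960) = Φ(1.373) = 91.5%. The t-test version gives 91.0%.

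The 95% CI half-width for the mean difference is 1.96 × 15 × √(2/50) = 5.9 points.

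**3. Lung function dichotomised.** For a cut at c control SDs from the control mean, p₁ = Φ(c) in controls and p₂ = Φ(c + 0.667) in cases. With p̄ the average of the two:

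Power = Φ{[(p₂ − p₁)√50 − 1.960 √(2p̄(1 − p̄))] / √(p₁(1 − p₁) + p₂(1 − p₂))}

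| Assumed cut | Controls below | Cases below | Power, 50 per group | Per group for 90% power |
|---|---|---|---|---|
| 2.5th percentile of controls | 2.5% | 9.8% | 33% | 226 |
| 5th percentile | 5.0% | 16.4% | 45% | 153 |
| 10th percentile | 10.0% | 26.9% | 59% | 109 |
| 1 SD below the control mean | 15.9% | 36.9% | 67% | 90 |
| Control median | 50.0% | 74.8% | 73% | 79 |
| Midpoint of the two means | 36.9% | 63.1% | 75% | 75 |

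At the 5th percentile, simulation gives 47% (pooled z) to 50% (likelihood ratio), close to the formula. Fisher's exact test gives 31%.

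Expected events at that cut: 50 × (0.050 + 0.164) = 10.7. A model with the group term and only two confounders would have 10.7/3 ≈ 3.6 events per coefficient.

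**4. TB status as the dependent variable.** In 2,000 simulated data sets with 50 per group, logistic regression of TB status on continuous lung function rejected in 91.6% (Wald) and 92.5% (likelihood ratio). The t-test on the same data rejected in 92.2%, so power is kept. With equal normal SDs the log odds ratio per SD lower equals d, giving exp(0.667) = 1.95. That is an odds ratio for TB per SD of lung function, not a difference in lung function.

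**The case against.** *Logistic* may be a slip for *linear*, since the same section handles spirometry through means elsewhere. That is possible, but the published text names the logistic model, and a slip of this kind still has to be corrected.

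The unseen analysis plan might define a binary outcome, and abnormal versus normal is a recognised way to describe lung health. This supports a secondary analysis. It does not reconcile a model for a binary outcome with a sample size for means, and both of those stand in the article.

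With TB status as the dependent variable, the test of association is intact. This stands: the objection to that reading concerns only what is estimated.

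The comparison is not among the three numbered study objectives, the first of which concerns imaging and lung function in adolescents with TB. That is also true, but it is the contrast from which the group sizes were derived.

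A reader might go further in four ways that the documents do not support:

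- *Most of the planned power is lost.* This depends on a cut-off that the article does not give. At the 5th percentile about half is lost, at more central cuts much less, and with TB status as outcome essentially none.
- *The fixed 1:1 ratio spoils the odds ratio.* Sampling on the outcome changes the intercept of a logistic model and leaves the odds ratios intact.
- *This is the only adjusted case-control analysis.* The article also plans multivariable comparisons of cytokines between the groups.
- *Household sharing is ignored.* The *Recruitment process* section does say that "the contacts of the enrolled cases will also be eligible for inclusion". However, the article is silent on variance estimation, which an analysis plan commonly covers. The effect would be small and could go in either direction.

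**Conclusion.** Wrong as written. The named model does not produce the adjusted lung-function deficit under either reading, and it does not match the comparison of means that underlies the 47 per group. That mismatch follows from the text alone.

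The cost in power is conditional. With a dichotomised outcome, power at 50 per group is 33% to 75% instead of about 91%, and about 45% at the 5th percentile, where the roughly 11 expected events leave little room for adjustment. These figures rest on normality, a common SD, the plan's shift of 0.667 SD and cut-offs assumed here. A composite outcome of any abnormality could yield more events. With TB status as the outcome, the loss is in interpretation and not in power.

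**What to change.** In *Assessment of study endpoints/primary objectives*, replace the logistic model with multivariable linear regression. The lung-function z-score is the outcome, TB group the exposure and the confounders the covariates. Where no z-score exists, use the raw value and add age, sex and height as covariates. Report the adjusted mean difference with its 95% CI.

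Logistic regression may stay as a secondary analysis if its outcome is defined in advance, for example as a value below the lower limit of normal.

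The cost is a change of wording. No new lung-function measurements are needed and the planned 50 per group can stand, because the sample size was already calculated for a difference in means.

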### Imaging

All adolescents with TB disease will undergo chest radiography (posteroanterior and lateral) as part of the standard routine care at baseline and will also undergo further chest X-rays (CXRs) at 2 months and 12 months. Those exposed to TB will have a baseline CXR only. Individuals with TB disease will undergo ultrasound at 2 weeks and 2 months, performed by trained medical personnel and using standard operating procedures. Ultrasound examination will include an evaluation of the chest, the abdomen and the mediastinum (through the suprasternal notch) and will be performed using two portable ultrasound machines—the Butterfly IQ and the Mindray DP 10. Two weeks into treatment, ^18^F-FDG PET-CT imaging will be performed for all adolescents with TB disease at the NuMeRI Node for Infection Imaging of SU. This will be carried out using a Vereos Digital PET 64-channel CT scanner (Philips Medical Systems) with a dose-sparing acquisition protocol. Participants will be fasted for 4–6 hours prior to the administration of FDG, which will be administered via an intravenous cannula, using universal precautions and aseptic techniques.

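### The imaging comparison against CT asks about diagnostic accuracy, but the contingency tests named for it, in their usual sense, test only association

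*Protocol article*

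**What the plan says.** The section Assessment of study endpoints/primary objectives states the radiology aim: "we will evaluate the ability of CXR and lung ultrasound to identify findings as seen on CT chest". CT is "considered as the imaging ‘gold standard’ for this analysis". The methods given are "using either contingency tests or receiver operating characteristic (ROC) analysis, where appropriate". The article does not say which contingency test is meant or which findings go to which method. Sensitivity, specificity, predictive values and agreement are not mentioned anywhere in it.

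CT is available only in the TB disease group. The Imaging section says: "Two weeks into treatment, ^18^F-FDG PET-CT imaging will be performed for all adolescents with TB disease". Table 2 shows the same. The planned size is given under Power and sample size: "we plan to recruit 50 cases and 50 controls". The comparison therefore rests on at most 50 patients. That number was not chosen for imaging: "we calculated the sample size based on ability to detect differences in lung function".

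**The concern.** Asking how well an index reading identifies what a reference standard shows is a question of diagnostic accuracy. It is answered by the proportion of CT-positive patients who are detected and the proportion of CT-negative patients who are correctly cleared.

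A chi-squared or Fisher test on the 2x2 table asks something else, namely whether the reading and CT are statistically independent. Rejecting independence does not show that the modality finds the lesion. Failing to reject it does not show that the modality misses the lesion, particularly when nearly all patients, or very few, have the finding on CT.

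If the sentence were followed literally and the p value reported as the result, a modality with poor detection could be described as significant and a sensitive one as non-significant. This bears on what the study can say about the value of simpler imaging compared with CT.

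**Working it through.** **The plan's own figure.** The only computed figure in the article is the lung function sample size, from "assumed to have a FEV1/FVC ratio of 100%; SD: 15"%, a case mean of 90%, 90% power and alpha 0.05 (taken as two-sided). n per group = 2 × (1.960 + 1.282)² × 15² / 10² = 47.3, which agrees with the stated 47 (48 if rounded up). It is not an input to the present point and is unaffected by it.

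**Inputs for the check.** n = 50 patients with CT is the planned number of cases. The cell counts below are assumptions for illustration, since the article gives none. TP, FN, FP and TN are counts of the index reading against CT.

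**Formulas.**
- Sensitivity = TP / (TP + FN); specificity = TN / (TN + FP).
- Exact (Clopper-Pearson) 95% limits for x out of n: lower is the 2.5% quantile of Beta(x, n − x + 1), upper is the 97.5% quantile of Beta(x + 1, n − x).
- Association: two-sided Fisher exact p for the 2x2 table.

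**Results.**

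| Assumed table (TP, FN, FP, TN) | Sensitivity (95% CI) | Specificity (95% CI) | Fisher p |
|---|---|---|---|
| A: 12, 13, 3, 22 | 12/25 = 48% (28% to 69%) | 22/25 = 88% (69% to 97%) | 0.012 |
| B: 5, 20, 18, 7 | 5/25 = 20% (7% to 41%) | 7/25 = 28% (12% to 49%) | 0.0005 |
| C: 44, 2, 3, 1 | 44/46 = 96% (85% to 99%) | 1/4 = 25% (1% to 81%) | 0.23 |

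**Reading.** In A the test is significant although 13 of 25 CT-positive patients are missed. In B it gives the smallest p value of the three although the readings are worse than chance: sensitivity + specificity − 1 = 0.20 + 0.28 − 1 = −0.52. In C detection is high but p is far from significant, because only 4 patients are CT-negative and 3 of those are misread. That pattern is plausible for common findings, since every case has confirmed pulmonary TB. The ordering of the p values therefore says nothing reliable about accuracy. The sensitivity and specificity columns, with their intervals, show the position in each table and come from the same four counts.

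**The case against.** The strongest reply is that the article does not commit to a chi-squared or Fisher test. It names neither. The phrase stands in a sentence that sets an accuracy aim, declares CT the reference, offers ROC analysis alongside and leaves the choice to suitability. Read in that context, it may simply mean cross-classifying present/absent findings against CT, with ROC for graded ones, and sensitivity and specificity come straight from that table. A condensed article may also leave the choice of accuracy measures to the full protocol or an analysis plan.

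Much of this stands. A reader might infer that the plan cannot show diagnostic accuracy. The documents do not support that: it is true of an association p value, not of every analysis of a contingency table, and ROC analysis is a valid alternative already on offer. Nor is accuracy against CT one of the three stated study objectives.

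What the reply does not remove is that the article names tests for this aim, and in their usual meaning those tests address a different question. The point concerns a method that is stated, not detail left unsaid. If accuracy measures were intended, naming them takes one sentence.

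**Conclusion.** The concern holds as a low-severity mismatch between a named method and the aim it serves. It rests on reading contingency tests in the ordinary sense of tests of independence, and on the inference that present/absent findings are the ones they are meant for. The illustrative p values (0.012, 0.0005 and 0.23) depend on assumed cell counts. They show that p does not track accuracy; they do not predict what the study will find.

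Two further inferences should not be drawn. First, a reader might object that an unpaired test cannot compare chest X-ray with ultrasound in the same patients. The article plans to set each modality against CT and announces no head-to-head comparison. Second, a reader might fear that the 2-month ultrasound would be judged against the 2-week CT. Ultrasound is also scheduled at 2 weeks, and nothing says the later scan would be used. No power or sample size figure is affected.

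**What to change.** For each finding read as present or absent, replace contingency tests with sensitivity and specificity of chest X-ray, and separately of ultrasound, against CT, each with an exact 95% confidence interval. Keep ROC analysis for graded scores. If a head-to-head comparison of the two modalities is intended, say so; McNemar's test, done separately in CT-positive and CT-negative patients, would then be suitable. Otherwise it is not needed.

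The cost is a change of wording, using the same data and the same 2x2 tables. The drawback is that with at most 50 cases, split by CT status, the intervals will be wide. In table A the interval for sensitivity spans about 41 percentage points (28% to 69%). Showing that imprecision is preferable to a bare p value that hides it.
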